# BACKGROUND and rationale

## 3.1 Background

The laying of a naso-gastric tube (NGT) is an extremely common procedure performed in intensive medicine; although the standard NGT insertion is performed at the patient's bed, this procedure is not free of risk. In this setting, serious complications can occur, especially in the sedated, intubated and curarized patient, which does not present the cough reflex; for example, complications in the placement of NGT in the lungs could be consequent potential pneumothorax, pneumonia *ab ingestis*, development of a bronco-pleural fistula, alveolar hemorrhages, etc. Some studies show an incidence of complications in the NGT pose in around 1% of total insertions, which are associated to a high morbidity, leading to an increase of hospital stay, global mortality and health costs (1-8, 10-11, 13-14, 16, 19, 21-24, 36, 38, 45, 53-56, 63-65, 67-69).

Numerous methodologies have been evaluated to recognize the correct positioning of NGT at the gastric level, including different clinical techniques (such as gastric auscultation, fluid from the NGT), ultrasound techniques, etc (7, 15, 18, 39-40, 43, 62). Actually, the diagnostic gold standard is the thoraco-abdominal anterior-posterior radiography, which is considered the only non-invasive method capable of confirming the correct NGT pose at intra-diaphragmatic level. However, this non-invasive method requires the use of ionizing radiation (4 uSv for radiography) which could be repeated multiple time for the same patient. As NGT may need to be repositioned several times during the same hospital stay, will be increase ionizing radiation patient exposure. Moreover, there could be an increase to ionizing radiation exposure for health workers too.

Furthermore, in sedated and intubated patients, the detection cassette is placed under the back. As some patients is hemodynamic or respiratory unstable, the required mobilization in order to place the detection cassette in situ, appears to be a further risk.

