## 3.2 Project rationale and significance

Through the use of methods already adopted in clinical field, we want to collect the values of the etCO2 from the trachea and the pH when the NGT is well positioned in stomach. . There are two methods, already present at clinical level but that need to be implemented: the capnometer and the pH-meter.

The use of the graphic capnometer (capnography) has already been demonstrated to be useful for detecting the positioning of the NGT at the tracheal level (7, 33, 61, 27, 18), even if today there are no studies able to show what is the "threshold level" of the detected CO2 to say with high specificity that NGT is certainly found in the airways (25-27, 31, 33-35, 37, 44, 46, 58-59, 61).

Furthermore, the use of the pH meter has already been remarkably demonstrated to be useful in analyzing the different pH levels in the proximal gastro-enteric tract, with differences between the stomach and the esophagus, even if there are no studies in this sense to identify the "threshold level" below which the pH certainly appears to be a gastric and non-esophageal pH (41-43, 50, 52, 60).

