# Study OBJECTIVES and Design

## 4.1 Primary and secondary endpoints

The primary endpoint is to identify the threshold value in the distribution and in the frequency of etCO2 and pH values. The pH values will be compared with the performed X .

The threshold values for etCO2 and for pH will be determined in two groups: group A, with the aim to find a threshold value of etCO2 above which we can be sure that aspiration probe is in the trachea and group B, with the aim to find a threshold value of pH below which we can be certain that NGT is in the stomach.

Further secondary results are expected:

- for patients in group A it will be necessary to perform a sub-analysis for the threshold value in the group of patients suffering from COPD;

- for patients in group B, a sub-group analysis will be performed for the threshold value for patients taking proton pump inhibitors (PPIs), and / or in the presence of an already diagnosed gastro-esophageal reflux disease.

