## 4.3 Study intervention

Group A procedure:

Patients needing the installation of a NGT at the Clinica Luganese Moncucco are consecutively enrolled and selected according to the inclusion and exclusion criteria listed below. The enrolled patients, after receiving adequately protocol study explanation and signed the informed consent, are sedated and intubated according to the clinical indications and the local protocols, independently from the ongoing study.

Anaesthesia is performed by a professional anaesthesiologist and an anaesthetist nurse, using standardized procedures according to local routine protocols. Induction and intubation therefore take place independently of the ongoing clinical study, independent from both indications for intubation, the choice of drugs and intubation material. At the end of the procedure, as usual, the secretions are aspirated with a suction tube of 18 Fr of 6mmdiameter. When the tube is inserted into the endotracheal tube, before proceeding with the aspiration of the secretions, a capnometer is attached to its outer end (picture A), measuring the etCO2 value for 10-15 seconds. At the end of the measurement, we proceed with the aspiration of the secretions as usual.

[figure not shown]
Pic. A

We then proceed with the laying of an NGT according to local protocols. Also in this case, once the NGT has been inserted, the etCO2 is measured at the end of the probe (pic A) for 10-15 seconds and its value is recorded in the CRF. At the end of the measurement, the capnometer can be detached, as a standard procedure, and the NGT can be used as usual.

At the end of the procedure, therefore, for each patient, two values ​​of etCO2 are acquired which will allow to obtain two "populations of values" of the etCO2: the values recorded ​​at the endotracheal level and the one recorded at the esophageal level. Through statistical analysis, we will find the "threshold value" above which the value of etCO2 found is certain for a location in the trachea. The expected mean values of etCO2, according to the literature, are 40 mmHg in the trachea (range 35-45 mmHg) and <25mmHg in the esophagus.

Group B procedure:

The group B enrolment will start at the Regional Hospital of Bellinzona. The enrolled patients are sedated and intubated according to the clinical indications and the local protocols, independently from the ongoing study.

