## 5.5 Study procedures

Peri-procedural evaluations

• Before anaesthesia;

• Patient eligibility (inclusion / exclusion criteria);

• Patient registration and recording of clinical and demographic data (height, weight, BMI);

• Anonymization by alpha / numeric code;

• Vital parameters recording: non-invasive arterial pressure, heart rate, respiratory rate.

- Group A patients (Clinica Luganese Moncucco):

• Clinical parameters recorded: COPD diagnosis, pulmonary embolism heart disease;

• Study parameters recorded: endotracheal etCO2, esophageal etCO2.

- Group B patients (Regional Hospital of Bellinzona):

• Clinical parameters: diagnosis of jatal hernia, intake of proton pump inhibitors (PPI), fasting hours, presence of reflux disease, enteral feeding;

• Study parameters: esophageal pH (25 cm from the dental arch), gastric pH (40 cm from the dental arch).

Study duration: 1 year (there is no follow up), including a recruitment period of 12 months

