## 8.2 Risk-benefit assessment

This study consists in several parameters collection in patients who required a NGT positioning. Thus, any potential clinical risk is related only to the standard procedure of NGT placing.

There will be no immediate benefits to the enrolled patients. Future patients who required a NGT positioning could benefit due to the potential of using threshold values as predictors of correct NGT placing, offering better treatment approach which not required thoracic-abdominal anterior-posterior radiography as diagnostic gold standard.

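### The thresholds are said to make tube location certain, but one reading at each of two known sites supports only sensitivity, specificity and likelihood ratios

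*Protocol*

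**What the plan says.** Section 4.1 sets the primary aims. For group A it wants a "threshold value of etCO2 above which we can be sure that aspiration probe is in the trachea". For group B it wants "a threshold value of pH below which we can be certain that NGT is in the stomach". Section 4.3 repeats the group A aim as a value "above which the value of etCO2 found is certain for a location in the trachea", but for group B it calls a low pH only suggestive of a gastric position.

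Section 3.2 puts the gap in the literature differently: no study gives a CO2 level "to say with high specificity that NGT is certainly found in the airways".

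Each patient contributes one reading per site. Section 5.5 lists for group A: "Study parameters recorded: endotracheal etCO2, esophageal etCO2". Group B has one oesophageal and one gastric pH.

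Section 6.2 names a one-sided z-test of two proportions at 0.01 as the step that identifies each threshold. Section 8.2 and the synopsis look ahead to the "potential of using threshold values as predictors of correct NGT placing" in future patients, without radiography. The only event rate given is in the synopsis and 3.1: "Some studies show an incidence of complications in the NGT pose in around 1% of total insertions".

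**The concern.** Being sure of the location given a reading is a post-test probability. It depends on sensitivity, on specificity and on how often a tube is in that location. Here the investigator fixes the location, and each site supplies half of the readings. Nothing in the design or in 6.2 carries the result to the frequencies met at the bedside.

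A significant z-test shows that the sites differ. If the plan is followed as written, that test could stand behind a claim of certainty that it does not support. The two groups would be affected differently:

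- **Group A.** The tracheal position is the uncommon one in practice, so a modest false-positive rate can outweigh the true positives.
- **Group B.** The gastric position is the common one, so the predictive value of a low pH is high almost whatever the test does. It says little about how many badly placed tubes would be accepted.

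**Working it through.** **Inputs from the protocol.** Evaluable patients: 35 in group A and 30 in group B (6.1). Readings: one per site per patient (4.3, 5.5). Expected etCO2: trachea 40 mmHg (range 35-45), oesophagus below 25 (4.3). No oesophageal SD and no misplacement rate are given.

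**Plan's own figures.** 35/(1 − 0.10) = 38.9, so 39 against 40 enrolled. 30/(1 − 0.10) = 33.3, so 34 against 35. Both agree closely. The base figures of 35 and 30 cannot be reproduced, because no pair of proportions is stated. The argument below uses them only as counts of readings.

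**Group A, best possible result: 0 of 35 oesophageal readings above the cut-off.**

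One-sided 95% upper limit for the false-positive rate (FP): 1 − 0.05^(1/35) = 8.2%.

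Predictive value for trachea, with p the share of tubes in the trachea: PPV = p·sens / [p·sens + (1 − p)·FP]. With sensitivity 1 and FP 8.2%:

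| p (assumed) | Calculation | PPV |
|---|---|---|
| 50% (study mix) | 0.5/(0.5 + 0.5 × 0.082) | 92% |
| 5% | 0.05/(0.05 + 0.95 × 0.082) | 39% |
| 1% | 0.01/(0.01 + 0.99 × 0.082) | 11% |
| 0.5% | 0.005/(0.005 + 0.995 × 0.082) | 5.8% |

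With a two-sided 95% limit, specificity could be as low as 90.0%, and PPV is 90.9% at 50:50 and 9.2% at 1%.

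**Separating prevalence from sample size.** Suppose the true FP were known to be exactly 1%. PPV is then 99.0% at 50:50 but 0.01/(0.01 + 0.99 × 0.01) = 50.3% at p = 1%. So the dependence on p remains when the cut-off's error rate is known, as long as that rate is not zero.

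**When would most high readings be false?** PPV falls below 50% when FP exceeds p·sens/(1 − p). At p = 1% and sensitivity 95% this is 0.0095/0.99 = 0.96%, so specificity must be below about 99.0%. At p = 5% it must be below 95.0%. To exclude a specificity below about 99.0% with no false positive takes about ln 0.05/ln 0.9899 = 295 oesophageal readings. The plan has 35 to 40.

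**How much overlap might there be?** Take a cut-off of 35 mmHg for illustration only, and read the tracheal range as a 95% range (sensitivity 97.5%). Assume a normal oesophageal distribution with SD 5. At p = 1%:

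- mean 15: PPV 99.7%
- mean 20: FP 0.135%, PPV = 0.00975/(0.00975 + 0.99 × 0.00135) = 88%
- mean 25: FP 2.275%, PPV = 0.00975/(0.00975 + 0.99 × 0.02275) = 30%

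The answer turns on a spread that the protocol does not state.

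**Group B.** With sensitivity and specificity of 95%, the predictive value for stomach is 95.0% at a 50:50 mix and 99.9% if 99% of tubes are gastric, so it rises. A cut-off that passes 90% of readings at both sites, and so does not discriminate, still gives 0.9 × 0.99/(0.9 × 0.99 + 0.9 × 0.01) = 99.0%. The useful figure is the share of oesophageal readings below the cut-off. With 0 of 30, its one-sided 95% upper limit is 1 − 0.05^(1/30) = 9.5%.

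**The case against.** The strongest reply is that this is mostly wording. Section 3.2 speaks of high specificity, which does not depend on prevalence and which the design can estimate. Section 4.3 describes two populations of values, and 6.2 compares sites; neither uses the 50:50 mix. Accuracy measures with limits might appear in a statistical analysis plan that is not at hand. The benefit statement in 8.2 is hedged. The low predictive values come from a confidence limit, and on the protocol's expected values the sites barely overlap.

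Much of this stands, and it rules out several inferences that a reader might draw:

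- **That the plan will compute a predictive value from the pooled readings.** No section says so.
- **That 1% is the misplacement rate.** It is an incidence of complications. No misplacement rate is given, so 1% can serve only as one assumed value in a range.
- **That a high etCO2 reading would usually be a false alarm.** At an assumed 1% that needs a true specificity below about 99%. The study might find better.
- **That group B suffers in the same way.** Its predictive value goes up in practice, not down.

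What remains is the stated aim. Sections 4.1 and 4.3 promise certainty of location, and 6.2 offers a two-proportion z-test as the route to it. A separate analysis plan could add accuracy measures, but the protocol's endpoint would still claim more than they can show.

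**Conclusion.** The point holds in a limited form. The study can estimate sensitivity, specificity and likelihood ratios at a cut-off. It cannot show how certain a location is in practice.

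In group A, a flawless result in 35 patients is still compatible with a predictive value anywhere from about 6% to 39% over assumed tracheal misplacement rates of 0.5% to 5%, against 92% at the study's mix. These are values at the 8.2% upper limit with sensitivity 100%, not forecasts: if the sites hardly overlap, the true predictive value could be high. In group B the predictive value for stomach is uninformative when most tubes are well placed, and up to 9.5% of oesophageal readings could fall below the cut-off even after 0 of 30.

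The protocol is also inconsistent on strength: certain in 4.1, suggestive in 4.3 for group B, high specificity in 3.2.

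**What to change.** - In 4.1, 4.3 and 6.2, replace the language of certainty by sensitivity, specificity and likelihood ratios at the chosen cut-off, each with exact 95% limits.
- State that predictive values will not be read from the 1:1 study sample.
- Show post-test probabilities only in a small table over a stated range of assumed misplacement rates, for example 0.5%, 1% and 5%, labelled as assumptions.
- For group B, make the share of oesophageal readings that would pass as gastric the main figure, with its upper limit.
- Bring 4.1, the group B text of 4.3, the benefit statement in 8.2 and the synopsis to one strength of claim.

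The cost is protocol wording plus one table from data already being collected; no extra patients or measurements are needed. The downside for the sponsor is that the stated certainty becomes less favourable.

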# STUDY SYNOPSIS

| **Project Leader** | [name]. [name]  Clinica Luganese Moncucco  [name]  [contact]  email: [contact] |
| --- | --- |
| **Study Title** | Tracheal etCO2 level and gastric pH level measurements as markers to confirm during the correct naso-gastric tube placement in unconscious patients. A physiological, prospective, observational study |
| **Study ID** | CLM_ICU_001 |
| **Protocol Version and Date** | Version 2, 31 Dec 2019 |
| **Risk Categorisation** | Risk category A according to HRO Art. 7 |
| **Study Design** | Prospective, observational study |
| **Project Design** | A multisite, prospective, observational, study in patients who required a NGT placement.  Group A: etCO2 measurement will be collected 1. after intubation, when the tube is inserted into the endotracheal tube, before proceeding with the aspiration of secretions and 2. once the NGT has been inserted, by a probe located at the end of the tube  Group B: pH measurement will be collected at the end of the procedure, once the NGT is inserted, at 1.a distance of 25 cm from the mouth (esophageal site) and at 2. a distance of 40 cm (gastric site), aspirating the gastric contents and measuring on specific litmus paper.  Group A will be done entirely in the Clinica Luganese Moncucco while group B in the Regional Hospital of Bellinzona. |

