Anaesthesia is performed by a professional anaesthesiologist and an anaesthetist nurse, using standardized procedures according to local routine protocols. At the end of the procedure, once the NGT is inserted, the pH is measured by aspirating the gastric contents and measuring on specific litmus paper the pH values, both at a distance of 25 cm from the mouth (esophageal site) and at a distance of 40 cm (gastric site).

At the end of the procedure, for each patient two values ​​of pH are acquired which will allow to obtain two pH "value populations": a value at esophageal level and a value at the gastric level. Through statistical analysis (see Section 6), we will try to find the "threshold value" below which the pH is suggestive for a localization in the gastric area.

The expected mean values of pH are 3.8 in the stomach (range 3.2-4.4) and 8.5 in the esophagus (range 6-9.5).

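### Group B labels pH readings esophageal or gastric by fixed 25 and 40 cm depths, with inconsistent oral reference points for a nasal tube and no working check that the 40 cm reading is gastric

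*Protocol*

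**What the plan says.** **Depths and reference points.** The group B procedure in Section 4.3 takes two readings per patient, "both at a distance of 25 cm from the mouth (esophageal site) and at a distance of 40 cm (gastric site". The synopsis (Project Design) says the same: "a distance of 25 cm from the mouth (esophageal site) and at 2. a distance of 40 cm (gastric site". The parameter list in Section 5.5 keeps the two numbers but changes the origin: "esophageal pH (25 cm from the dental arch), gastric pH (40 cm from the dental arch".

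**Route and sample.** The tube is naso-gastric in the title and throughout (Section 3.1). No section gives a distance from the nostril. Section 4.3 describes the sample in one phrase that covers both readings: "once the NGT is inserted, the pH is measured by aspirating the gastric contents and measuring on specific litmus paper the pH values".

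**Patient factors.** Section 5.5 provides for "recording of clinical and demographic data (height, weight, BMI", but height plays no part in setting the depth.

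**Use of the readings.** Section 4.3 turns the two readings into two populations of pH values, from which the threshold is to be found. Section 4.1 wants a value below which gastric position is certain.

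**Check on position.** Section 4.1 has one sentence, cut short in the text at hand: "The pH values will be compared with the performed X". Since Section 3.1 names radiography as the gold standard, I read this as an X-ray. An X-ray is not mentioned in the group B procedure (4.3), the parameter list (5.5), the analysis section (6.2) or the schedule in Appendix 1.

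**The concern.** A threshold study needs a reference standard: each reading must be known to come from the site it is said to represent. Here the depth mark serves as that standard. If some 40 cm readings are not from the stomach, the population called gastric is a mixture, and the threshold derived from it describes the mixture. This can happen with perfect adherence, because the label follows from the rule and not from where the tip lies.

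The reference points add a second problem. Staff have two written origins for the same numbers, and neither is where a nasal tube enters the body. Section 4.2 has all staff taking measurements on the ground that they do not depend on the operator. How a depth is read from an unsuitable landmark does depend on the operator. Sampling depth is not among the parameters recorded in Section 5.5, so a discrepancy could not be found or corrected afterwards.

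**Working it through.** **1. The passages side by side**

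| Place in protocol | Esophageal | Gastric | Counted from |
|---|---|---|---|
| Synopsis, Project Design | 25 cm | 40 cm | mouth |
| 4.3, group B | 25 cm | 40 cm | mouth |
| 5.5 | 25 cm | 40 cm | dental arch |

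Within each place one origin appears to serve both depths; the conflict is between places. The protocol does not say how far apart the two origins are.

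**2. Share of 40 cm readings at or above the junction**

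The protocol gives no junction depth. Assumption: depth from the oral landmark is normal with mean μ of 37 to 42 cm and SD σ of 2 to 3 cm. The share is 1 − Φ((40 − μ)/σ).

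| μ (cm) | σ = 2 | σ = 3 |
|---|---|---|
| 37 | 7% | 16% |
| 38 | 16% | 25% |
| 39 | 31% | 37% |
| 40 | 50% | 50% |
| 42 | 84% | 75% |

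The range, 7% to 84%, is set almost entirely by the assumed mean.

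**3. Effect on the threshold**

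Inputs from the protocol: stomach 3.8 (3.2–4.4) and esophagus 8.5 (6–9.5) from Section 4.3; esophagus about 7 (5–8) from Section 6.1. The two esophageal figures differ, so both are run. Reading each interval as a 95% range gives these SDs:
- stomach: 1.2/3.92 = 0.31
- esophagus: 3.5/3.92 = 0.89, or 3/3.92 = 0.77

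Further assumption: a mislabelled reading has esophageal pH. Let m be the mislabelled share.

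*Cut-off capturing 95% of readings labelled gastric.*
- m = 0: 3.8 + 1.645 × 0.31 ≈ 4.3. Almost no esophageal readings fall below it.
- m = 10%: solve 0.90 + 0.10 × F(t) = 0.95, where F is the esophageal distribution. F(t) = 0.50, so t is the esophageal mean: 8.5 or 7.0. Half of esophageal readings fall below it.
- m = 20%: 0.80 + 0.20 × F(t) = 0.95, so F(t) = 0.75. Three quarters fall below it.
- m = 7%, the low end of step 2: 0.93 + 0.07 × F(t) = 0.95, so F(t) = 0.29 and t ≈ 8.0 or 6.6.

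*Apparent sensitivity at a fixed cut-off.* Take 5.5, the value from a cited trial in Section 3.1. The share of readings labelled gastric that fall below it is (1 − m) + m × F(5.5). F(5.5) is close to 0 for a mean of 8.5 and 0.025 for a mean of 7. At m = 10%, 20% and 30% the result is about 90%, 80% and 70%.

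**4. Would the planned test show it?**

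Section 6.1 plans 30 evaluable patients, one-sided alpha 0.01 and 90% power, and registers 35. The inflation is in order: 30/0.9 = 33.3, or 34 patients. The base of 30 cannot be re-derived because the two proportions are not stated, but nothing here depends on it.

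Compare the proportions below 5.5 by the two-proportion z-test with 30 readings per site. Power is practically 100% at m = 10% and still at least 99% at m = 50% (0.50 vs under 0.001, or 0.51 vs 0.025). A significant result says nothing about whether the labels are right.

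**The case against.** The strongest objection is that the consequence is not in the documents. No section gives a junction depth, and a range of 7% to 84% measures ignorance more than error. That stands. A reader might infer that many, or most, 40 cm readings are really esophageal; the protocol does not support this, and no minimum number of mislabelled patients can be derived from it.

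Two further inferences should also be resisted. One is that 40 cm would be read at the nostril, leaving the tip higher still: the text names the mouth or the dental arch, and gives no figure for the difference. The other is that hiatal hernia, recorded in Section 5.5, makes the 40 cm reading less gastric: nothing in the protocol supports that direction of effect.

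It can also be said that Section 4.1 supplies a check. It does name a comparison, and the cut sentence may have been fuller in the source. But the comparison is not carried into procedures, recorded parameters or analysis. A film of the tube as placed confirms the 40 cm sample only if the tube is left at 40 cm, which group B does not state. A separate analysis plan could add an exclusion rule, but it could not supply positions and films that the study did not record.

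Mouth and dental arch are close, so the wording conflict alone is probably minor. The missing nasal reference and missing confirmation weigh more.

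Finally, step 3 assumes fully esophageal pH in every mislabelled sample, and a cut-off set from the esophageal readings would not shift in this way. Both points stand; in the second case the loss appears as lower apparent sensitivity.

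**Conclusion.** The point holds in this form. The site labels that act as reference standard for the primary group B threshold are set by fixed depths, counted from origins that differ between sections and do not suit a nasal tube, and no stated rule verifies them. This follows from the protocol alone.

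The size of the harm does not. The 7% to 84% range rests on an assumed junction depth, and the shift in cut-off from about 4.3 to 7.0–8.5 at 10% mislabelling rests on the further assumption of esophageal pH in mislabelled samples. What can be said is that a share near the low end would already matter for a cut-off chosen to capture 95% of gastric readings, and that the planned z-test would not reveal it. It should be settled before enrolment, because unrecorded depths cannot be recovered.

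**What to change.** - **Synopsis, 4.3 and 5.5:** reconcile to one reference point that fits a nasal tube, and restate both sampling positions against it, the esophageal one included. Which positions these are is for the investigators to decide.
- **4.3:** take the reading labelled gastric at the tube's as-placed position under the local protocol, so that the sample and the film refer to the same position.
- **5.5 and the CRF:** record the depth of each reading and the X-ray result.
- **4.1 and 6.2:** state that the gastric label is confirmed by the X-ray Section 4.1 appears to mention. Leave unconfirmed readings out of the threshold analysis, or show the threshold with and without them as a sensitivity analysis.

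The cost is amendment wording and a few CRF fields. No extra procedure should be needed if the film is taken in routine care, as the wording of 4.1 suggests, but the protocol does not say that every group B patient has one, so this should be checked. Gastric sampling depth will vary between patients, which is why it is recorded, and a few readings may remain unconfirmed.
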